#### Feasibility

The pilot study leading up to the current study [62] had a high retention rate (no dropouts), the patients showed a high degree of compliance. Filling in outcome self-report measures was feasible with the help of the translators. Recruitment took place in cooperation with the physician in only one clinic. In the current study, three locations with 250–300 patients per year are included, and there are 1.5–2 years to recruit 70 participants. The potential participants are screened for eligibility already during the clinical visitation process. We are aware that music therapy is a new treatment option that can seem difficult to understand by some patients, that the randomization process has to be explained carefully and that participation in a research study can be a stress factor for traumatized patients. We assume that the feasibility of performing a RCT within the chosen framework will be reasonable.

## Interventions

The refugee clinic carries out trauma treatment in a multidisciplinary clinical setting. The current study compares only the psychotherapeutic part of treatment, but for ethical reasons all other services (social counseling, body therapy, health advice) in the clinic are kept open for all participants as needed, and the extent of other services will be monitored throughout the study. All participants who receive medication as part of the treatment in the experimental group as well as the standard treatment group are monitored continuously by the physicians during the whole course of psychotherapy. Differences between groups are analyzed as possible confounders related to outcome.

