
Adherence to treatment is monitored through the evaluation of sessions, and in case of dropout participants are asked about their reasons for stopping treatment, if possible. A research log including dropout information is kept by the researcher team. Additional sessions in the clinic during participation (such as body therapy or social counseling) and change of medication are followed in the patient journal and scored in the data collection environment.

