#### Randomization

Randomization is carried out with the help of the randomization software Sealed Envelope (https://sealedenvelope.com/). Stratification is applied regarding geography (three different locations) and gender (male/female). Within the strata, random permuted blocks of even length (blocks of four or six participants) are used. When a participant has given informed consent and completed baseline measures with one of the three music therapists who takes care of the research procedures (one in each location), the music therapist/researcher logs on to the randomization website and types patient ID number, gender and location. Information of the treatment group is provided immediately on the website and is also sent by email to the researcher. The status of the patient is typed into the Xpsy database, and the patient is referred to either music therapy or standard treatment at the location.

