### Risk of bias

In a psychotherapy trial such as this, it is often not possible to blind the intervention of the participants, and there can be an influence of their knowledge of being in the intervention or the control group. However, in this trial we investigate two types of treatment in a single clinic with equal dose (16 sessions) and equal weight as primary trauma treatment modalities. According to concealment of allocation, the randomization procedure is generated by computer software at Sealed Envelope, and none of the researchers have any influence over the procedure. Baseline tests are carried out before randomization, so that the allocation does not influence the measurement. Psychologists carrying out data collection concerning the primary outcome measure at post and follow-up times are concealed to the allocation (and the patients are not asked about it). Imbalances between treatment groups are prevented by the use of stratification (gender and location).

As music therapists carry out the information meetings and measurement, the participants might be more motivated for music therapy than standard treatment (comparator), and be more likely to drop out from standard treatment. This could possibly influence the results in favor of music therapy. Adherence to the treatment is secured, as none of the participants can cross over to the other group. If a patient drops out from music therapy and is offered standard treatment, they are excluded from follow-up. If participants are offered other types of treatment in the clinic parallel to the assigned treatment, this will be monitored and an analysis of any group differences will be carried out.

Protocol fidelity is assured by data collection of the therapist notes for all sessions, by team supervision and frequent meetings between music therapists and psychologists and in the group of music therapy researchers. The use of Xpsy for data collection ensures that no participant data are analyzed in the wrong group.

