Translators are used with participants, who find it beneficial. In a translated session, the verbal information passed is little less than half of that of a session without, as everything has to be said twice and quite often there is necessary conversation about the meaning of a single sentence. Consequently, the doses of therapy for participants with translators are not comparable to those without translators. There are often limits to the conversation with the translator, who might be a young and relatively inexperienced person with a limited vocabulary on matters relating to psychotherapy and trauma in either one of the languages used. Many of the Arabic-speaking participants do not have Arabic as their mother tongue. There is no officially approved education for translators, the clinic is not free to choose the best available translators, but is bound by an exclusivity contract with one vendor. Most of the translators are bi-lingual persons without any formal training as translator or any higher education in either language. The translator brings their own presence into the therapy room and the therapeutic dyad effectively becomes a triad. The official goal of the translator is not to be personally present, but in a psychotherapy session, where the implicit is just as important as the explicit, this becomes impossible, and the best implicitly present translator is the one who can join the atmosphere that develops in the session and not stick to a rigid pretence of not being there. It follows that translation alone is a complex phenomenon that influences outcome more for some clients and not at all for those who do not use translators. Furthermore, it perhaps influences music therapy and standard treatment differently.

The use of the interdisciplinary team during the course of treatment according to individual needs means that some participants receive more treatment than others, especially so for participants needing physiotherapy or body therapy (psychomotorical therapy). This is usually prescribed for patients having specific and disturbing physical symptoms. Also, advice from a social worker helps clarify issues with authorities and other professionals. The amount of extra treatment and counseling is monitored and recorded in each case.

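### Services and medication given during therapy are to be analysed as possible confounders, but they arise after randomisation; adjusting the non-inferiority comparison for them could bias it in either direction

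*Protocol article*

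**What the plan says.** Interventions states that social counselling, body therapy and health advice "are kept open for all participants as needed, and the extent of other services will be monitored throughout the study". Participants on medication in either arm "are monitored continuously by the physicians during the whole course of psychotherapy". The paragraph then gives these variables their analytic role: "Differences between groups are analyzed as possible confounders related to outcome".

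Three other places bear on this:

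- The adherence paragraph that follows Procedures says additional clinic sessions and "change of medication are followed in the patient journal and scored in the data collection environment", so the variables will be in the dataset.
- Risk of bias says of parallel treatment that "this will be monitored and an analysis of any group differences will be carried out".
- Limitations and complexities says "The amount of extra treatment and counseling is monitored and recorded in each case". It adds that the use of the team depends on individual need and that body therapy usually goes to patients with troublesome physical symptoms.

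On timing, the Randomization section starts the allocation step "When a participant has given informed consent and completed baseline measures with one of the three music therapists"; referral to the assigned therapy comes after it. Statistical methods adopts intention to treat and an ANCOVA for HTQ. It names no covariates.

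**The concern.** To confound a treatment comparison, a variable must influence which treatment is received. Here allocation is random and complete before any of this care is given, so the care cannot do that. It can follow from the assigned arm, from how the patient fares, or from needs present at baseline. A covariate model that includes it removes whatever part of the arm effect runs through it. It also opens a non-causal path, because among patients with the same amount of extra care, the arms may differ in prognosis.

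What is at stake is the primary claim. The margin is 0.3 HTQ points and the planned standard error is about 0.12, so a shift of a few hundredths changes the chance of declaring non-inferiority. An analyst who follows the Interventions sentence could enter service use and medication change in the ANCOVA, or hold both an adjusted and an unadjusted result with no stated rule for which one counts.

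**Working it through.** **1. Timing and drivers.** The order in the protocol is consent, baseline, randomisation, referral, therapy. Service use and medication change are recorded during therapy, so they come after randomisation. Provision is by need, so dependence on symptoms is likely. How far it depends on arm or on-treatment course is not known.

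**2. The plan's own figure.** Inputs from Power calculation: margin 0.3, SD 0.48, significance level 0.05 (sidedness not stated), power printed as 0.08 and read here as 0.80. With one-sided 0.05:

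n per arm = 2 × 0.48² × (1.645 + 0.842)² / 0.3² = 31.7, rounded up to 32, total 64.

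This reproduces the stated 64 and is not in dispute. It fixes the standard error: 0.48 × √(2/32) = 0.12.

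**3. What adjustment does.** For a linear model with a service variable M,

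adjusted difference = unadjusted difference − c × Δ,

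where Δ is the arm difference in mean M (music therapy minus standard) and c is the within-arm slope of HTQ on M. If Δ = 0, nothing changes. If Δ > 0 and c > 0 (extra care marks poor outcome), the music therapy deficit shrinks. If Δ > 0 and c < 0 (extra care lowers HTQ enough to outweigh that), it grows.

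**4. Illustration with yes/no service use.** All inputs in this step are assumptions: true deficit 0.30, latent course correlated 0.7 with outcome, log-odds of service use 1.0 or 1.5 per SD of course, services without effect of their own, use of 51–52% against 42–44%. The adjusted estimate is 0.279 or 0.264. The false non-inferiority rate is Φ((0.3 − estimate)/0.12 − 1.645):

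- 0.279: Φ(0.175 − 1.645) = 0.071
- 0.264: Φ(0.300 − 1.645) = 0.089

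Both compare with 0.05 unadjusted.

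**5. Letting the services work.** A graded service score was simulated with 32 per arm. It rises by γ per 0.48 HTQ points of mid-treatment symptoms, its random part has SD 1, and it changes HTQ by β per unit. Sixty percent of the HTQ variance is shared between the mid-treatment and final scores. The total effect is held at 0.30. γ and β are assumptions.

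| γ | β | Adjusted estimate | False non-inferiority |
|---|---|---|---|
| 0 | 0 to −0.3 | 0.30 | about 5% |
| 0.5 | 0 | 0.263 | 9.5% |
| 0.5 | −0.1 | 0.294 | 5.5% |
| 0.5 | −0.2 | 0.333 | 2.5% |
| 0.5 | −0.3 | 0.384 | 1.0% |
| 1.0 | 0 | 0.211 | 20.1% |
| 1.0 | −0.1 | 0.266 | 8.7% |
| 1.0 | −0.2 | 0.360 | 1.5% |
| 1.0 | −0.3 | 0.560 | 0% |

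Unadjusted, every row gives about 0.30 and about 5%.

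The formula in step 3 agrees. For γ = 0.5, β = 0: Δ = 0.5 × 0.30/0.48 = 0.3125 and c = 0.5 × 0.6 × 0.48/(1 + 0.25) = 0.115, so the adjusted value is 0.30 − 0.115 × 0.3125 = 0.264. In this model the bias changes sign where β = −0.288γ/(1 + γ²), that is −0.115 at γ = 0.5 and −0.144 at γ = 1.0.

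**The case against.** The strongest reply is that the protocol never says the primary estimate is adjusted for these variables. Statistical methods commits to intention to treat and lists neither services nor medication as covariates. The Risk of bias sentence reads naturally as a between-arm comparison of parallel treatment, and the Limitations sentence speaks only of recording. This is also a condensed article, and the covariate list may properly sit in an analysis plan that is not shown. All of that stands. A reader might infer that the trial has planned a biased primary analysis or has abandoned intention to treat; the document does not support that.

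A reader might also infer that the bias runs towards a false non-inferiority claim. That is not fixed either. It needs extra care to be mainly a marker of poor response, and the 7–9% figures assume that the services do nothing. They are offered as treatment. In the yes/no model of step 4, a service effect of about −0.3 HTQ roughly cancels the bias at log-odds 1.0; in the graded model the bias reverses. Some need, such as physical complaints or dealings with authorities, may also predate randomisation or have little to do with the assigned therapy.

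What the reply does not remove is the sentence itself. It is the only place that gives these variables an analytic role linked to outcome. Treating something as a confounder ordinarily means adjusting for it or stratifying on it. That role is wrong in kind for care given after allocation, whatever an analysis plan later adds.

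**Conclusion.** The point holds as a conditional one. The protocol classes post-randomisation, need-driven care as a possible confounder, which it cannot be in a randomised comparison. If that care is entered as a covariate in the non-inferiority analysis, the result no longer estimates the effect of assignment and may be off in either direction.

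The size depends on inputs the protocol does not give. Under the assumed scenarios, false non-inferiority at the margin goes from 5% to about 7–9% with yes/no use. In the graded model it reaches about 20% with strong targeting and inert services, and falls below 5% when the services lower HTQ appreciably. There is no bias if uptake is unrelated to arm and on-treatment course. The stated sample size is unaffected.

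**What to change.** Replace the Interventions sentence with wording such as: concomitant services and medication changes after randomisation are summarised and compared by arm and are not covariates in the primary non-inferiority analysis, which adjusts only for variables fixed before randomisation (baseline HTQ, location, gender). Add that any analysis accounting for concurrent care is a separate sensitivity or exploratory analysis and does not decide non-inferiority. Align the Risk of bias sentence with this by saying that its analysis of group differences is a comparison of care received by arm.

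The cost is a sentence or two. Data collection, sample size and patient care do not change.

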### Dose

A significant correlation between dose and response has been found for music therapy treatment with serious mental disorders, with small effect sizes after three to ten sessions and large effects after 16 to 51 sessions [66]. A review of quantitative studies of GIM concluded, that at least ten sessions should be provided for clinical populations [67]. In our pilot study, 16 sessions provided significant changes with large effect sizes on all the outcome measures. This number of sessions also fits with the psychiatric clinic’s standard length of treatment. We chose to repeat the 16 sessions as dose for both treatment arms in the present study.

The patients participate in weekly sessions, lasting 60 min. If any cancellations occur the treatment period is prolonged until all 16 sessions have been received. Should the participant encounter any given events that would lead to further traumatizing by way of circumstances outside therapy, treatment can be prolonged to as many as 20 sessions, after consultation with the treatment team and the physician. Hence, a margin of 25% is accepted (from 12 to 20 sessions). In both music therapy and the comparator treatment a phase-oriented treatment according to Herman [68] is carried out, including a stabilizing phase, a trauma-exposure phase and a reorientation phase (if possible). The development of a safe therapeutic relationship and verbal processing are components in both psychological standard treatment and trauma-focused GIM. Thereby, the professional adaptation of music as a therapeutic medium, including the way that music influences the therapeutic relationship, is the independent variable in the trial.

### Trauma-focused Music and Imagery (TMI)

TMI is an adaptation of GIM, a music therapy method initiated by the American music therapist Helen Bonny in the 1970s [53, 69] using music listening of selections of classical music in an altered state of consciousness as a medium for therapeutic change. During the listening experience, a non-directive verbal dialog between patient and therapist is carried out supporting the deepening and integration of the ongoing stream of imagery, emotions and sensations evoked by the music. GIM has served as primary psychotherapeutic treatment in a range of clinical settings and has been modified and adapted to several clinical populations [70]. A continuum of practices exists, from the full Bonny method (2-h sessions with challenging music and verbal dialogue) to short GIM (1-h sessions, shorter music selection); music and imagery being a supportive short-form that often only includes one or a few short music pieces and no verbal interaction during the music listening part.

A GIM therapist holds a master’s degree in music therapy or other relevant subject followed by a minimum of 3 years of supervised training in the GIM method licensed by an international training institute (see www.music-and-imagery.eu).. The method has been adapted to refugee trauma treatment by the authors [name], [name] and [name] [62].

A TMI session includes:A verbal conversation used to check in and talk about actual issuesAgreement of a focus for the music listeningFinding a music piece (patient chosen or therapist chosen; if the therapist chooses the piece a small excerpt is played to assess the match of music with the patient). Music from several genres are optional: classical, film, meditative music, or music corresponding to the patient’s cultural backgroundMusic listening; the patient is sitting on a chair or lying on a couch, eyes open or closed as preferredA short induction; for example, mindful focus on breathing, guided relaxation or focus on an inner imageMusic listening (2–10 min in the beginning, up to 20 min in the end of therapy). The therapist can talk during the music if helpfulThe therapist guides the patient back to the presentParticipants are invited to draw a picture of the imageryVerbal communication about the drawing and the experience with the focus on integration of important imagery, acknowledgement and meaningfulness in the therapeutic processHomework assignment as needed (including using music at home)

Treatment phases (the session numbers are indicative as a patient can stay in phase 1 for the whole time or go back and forth between phases):

#### Phase 1. Stabilization phase (sessions 1–5)

The participants are provided with a CD containing seven pieces of music for listening to at home (see Appendix 2). The preferred piece(s) is(are) used in the first sessions. The patient’s relationship with music is explored. Psychoeducative elements are introduced (such as understanding of PTSD symptoms and the autonomic nervous system in trauma). Music accompanied breathing [70] is offered as help to deepen the breathing (abdominal breathing) and to regulate arousal. Positive inner imagery such as “the safe place” and positive memories of close relatives or events before the war are presented as central to increase biopsychological resources and safety. Music as a safe ground and as a way to detach from pain and negative feelings is in the focus. The therapeutic alliance develops through shared experience with music. The music in the stabilization phase is characterized by a high degree of predictability concerning the musical parameters (i.e., a stable, slow tempo, only gradual changes in volume, rhythm, sound, register and harmony), simple dynamics (such as ABA) and use of repetition in melody and chords. The participant is asked to work with the music at home between sessions.

#### Phase 2. Emotional containment (sessions 6–8)

Contact with different kinds of emotions in the music is explored. Both positive and difficult emotions can be experienced, while listening to music, and the ability to contain contrasting emotions, ambivalence and different aspects of emotions are important parts of the investigation process. The primary focus is on giving the patients an opportunity to both explore and be able to stay with difficult emotions with the aid of music, as well as a possibility to develop new coping skills that will allow the patients to change their emotions through their interaction with the music. If the patient is stable enough and feels safe, music with more depth and dynamics can be introduced.

#### Phase 3. Trauma exposure and grieving (sessions 9–14)

A process of exposure during music listening is carried out when the patient has achieved sufficient stabilization. The narrative of traumatic events can be accompanied by, and supported by, music, or music and imagery can be used for exploration of traumatic episodes. Trauma imagery can also emerge during music listening without a fixed focus, and can be processed with the support of the therapist and the music. The music serves as a holding structure that match the emotions and states of trauma processing, or the music can be used to regulate arousal during exposure. All sessions are carried out with the focus on step-by-step work and safety; for instance, can music pieces connected to safety imagery or positive resources alternate with pieces of music accompanying trauma memory. Traumatic episodes can be renegotiated during music listening, meaning that the patient finds alternative solutions in imagery to a stuck situation in the past, and/or that incomplete defense actions (fight and flight) can be carried out in the imagination. Grieving and loss are common themes that are explored in the music and imagery experiences, and can be assessed by encouraging the patient to engage in imaginary dialog with lost relatives. Anger management can be included as a therapeutic focus.

If a patient is overwhelmed by the music and imagery experience, or suffers intruding flash-backs, the music is immediately turned down or changed. When possible, music from the patient’s own culture is evaluated by the interpreter before use to ensure that the lyrics and the traditional use of the piece is appropriate for the session.

#### Phase 4. Reorientation (sessions 14–16)

In phase 4 the patients are encouraged to develop their social network and engagement in activities in their community if they are ready for it. Music and imagery can help the patient to be reminded of their dreams, and to keep them in focus as a beacon for their goals in life. Moreover, the imagery can serve as a way to rehearse new kinds of behavior in a safe environment. This phase also touches on identity and existential meaning, and the chosen music stimulates the patient to reflect upon on these cornerstones of life. The therapy course is brought to a closure, and the focus is on how the patient can go on with their life.

The described protocol is adapted to the specific needs of the patients. In case the patient cannot tolerate music at all as part of being hypersensitive to sound (which can happen due to insomnia, pain or re-traumatization), there can be sessions with only verbalization and guided imagery without music. In case the music therapist suggests that live music would be a more adequate choice than recorded music in terms of attunement to the patient, or should the patient be more able to tolerate live music, the music therapist can use their own voice and musical instruments and create music on the spot to facilitate the inner experience of the patient (as there has been examples of in the pilot study). Accordingly, patients who can tolerate short GIM (longer music and verbal interaction during the music) are offered this option.

